### Patient Follow-up

At the baseline visit, patients will have a complete history and physical examination recorded including height, current weight, and weight 6 months prior. Patients will complete a baseline QoL assessment during their clinic visit (Multimedia Appendix 1 and Figure 1). Patients will be asked to complete a health resource utilization form at 15 and 6 days before surgery (Multimedia Appendix 1). Immediately after surgery, patients will be followed on a daily basis during their hospital stay to collect postoperative complications and compliance data and length of hospital stay (Multimedia Appendix 1). Following discharge from the hospital, patients will then be assessed at their first postoperative clinic visit 4 weeks (±1 week) following the index surgery. The second postoperative follow-up will happen at 12 weeks (±2 weeks) following surgery. At each assessment, a physical examination will be completed. A QoL questionnaire will be given to patients to complete while they wait in the surgical clinics. They will also be asked to complete a health resource utilization form at each assessment. Mortality will be recorded 90 days after surgery.

**Figure 1 figure1:**
[figure not shown]
Study schema. F/U: follow-up; HRU: health resource utilization assessment; MUST: Malnutrition Universal Screening Tool; OR: operating room (index surgery); POC: postoperative complication assessment; QoL: Quality of Life Assessment.

### Data Management

In addition to physical examination and QoL data, a research assistant will gather postoperative complication data from patients’ charts or electronic medical records and transcribe it on to CRFs, which will be updated daily while the patient is in the hospital. Before surgery, a compliance diary will be provided to patients to evaluate their adherence. Compliance data will also be collected from the nurses’ charts while the patient is in the hospital, with a specific CRF designed to record the volume of the supplement the patient has taken after surgery. The feasibility CRF will include reasons for two different processes: (1) reasons for not consenting and (2) reasons for not randomizing if the patient consented. Data will be stored in a secured electronic database at OCOG.

### Sample Size and Feasibility

Currently, there are 200 gastrointestinal resections performed annually for gastrointestinal cancer at JHCC (300 over an 18-month period). We expect at least 55.0% (165/300) patients to be eligible for the study. Additionally, we expect that 60.6% (100/165) eligible patients will be randomized to either intervention or placebo. Assuming a two-sided alpha of .05, this will give us a 95% CI around the estimate of 53.0%-68.0%. A sample size of 100 (50 per group) will enable us to estimate the treatment effect and corresponding variance of the complication rate, CCI, and QoL measures with adequate precision. Given the number of patients that undergo surgery at JHCC and the number of patients eligible for the study, we believe we can complete accrual to the study in 18-21 months. Given that the follow-up is 3 months, we expect the study to be finalized within 21-24 months of commencement.

### Statistical Analysis

Patient baseline characteristics and demographics by treatment group will be presented using descriptive statistics. The proportion of eligible patients randomized and its corresponding 95% CI will be calculated using the Wilson method. The criterion for success of this study is defined as the proportion of eligible patients randomized as ≥60.0% (60/100). If the estimated proportion is <40.0% (40/100), the trial will be considered not feasible. If the proportion is between 40.0% (40/100) and 59.0% (59/100), the trial will be considered feasible, with modifications to improve enrollment.

The difference in the proportions of any postoperative complication between groups and its corresponding 95% CI will be calculated using the Wilson method. The proportion of patients who are compliant with study therapy and 95% CI will also be calculated. Differences in compliance between treatment groups will be described. Good compliance will be defined as consumption of ≥70% (at least 41/58) sachets of the study intervention before and after surgery. If the compliance is ≥70% (at least 41/58 sachets), there will be no exploratory analysis to evaluate the reasons for noncompliance. Compliance of <70% (40/58 sachets or less) will be considered poor, and reasons for noncompliance will be further explored (eg, problems with the distribution or administration of the supplements, bad taste, side effects, inability to tolerate oral intake, etc) These reasons will be clearly stated in the compliance CRFs.

The mean (SD) of the CCI at 90 days from the index surgery will be estimated for each group, and the mean difference between groups will be estimated with its corresponding 95% CI. QoL scores will be summarized using means and corresponding SDs. The mean difference in the QoL scores between groups at 1 and 3 months will be estimated using linear models adjusting for baseline QoL scores.

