**Results:**

We expect to screen 165 eligible patients; 60.6% (100/165) of them will be randomized to either intervention or placebo. Assuming a two-sided alpha of .05, this will give us a 95% CI around the estimate of 53%-68%. A sample size of 50 per group will enable us to estimate the treatment effect and corresponding variance of the complication rate and QoL measures with adequate precision. The success is defined as the proportion of eligible patients randomized as ≥60.0% (60/100). Patients’ compliance is defined as an intake of at least 70% (41/58) sachets of the intervention volume.

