#### Protein Isolate Powder (ISOlution)

This will be consumed by the patient to increase muscle protein synthesis and achieve the recommended per meal protein intake prior to surgery as well as after surgery. Each serving delivers 20 g of protein stirred into a minimum of 250 mL of liquid or soft foods. Patients will be asked to consume 1 serving per day (20 g of protein powder in total per day) from the time of randomization up to 6 days before surgery (up to 30 days in total).

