At this point, patients will fill out a daily compliance diary from the date of randomization until up to 5 days after surgery. This compliance diary will be transcribed into a preoperative compliance case report form (CRF) that includes the number of packets the patient took every day, the volume that was ingested, the days it was ingested for, and the reasons patients were not compliant. While in the hospital, the nurses will be responsible for administration, as PReSS will facilitate the administration of the supplements (INergy-FLD) by adding them to the nursing care pathway of the patients. Compliance during this time will be obtained from the nurses’ log, which includes the amount of solution the patient ingested during each administration and the days the patient ingested the solution. If for some reason, the patients are unable to tolerate an oral diet (postoperative complications such as delayed gastric emptying, ileus or bowel obstruction, etc), the nurse will contact the principal investigator of the study and the order to suspend the administration of the solution will be assessed for each patient. This will be noted in the nurses’ chart and transcribed to the postoperative compliance CRF. Patients will continue to be part of the study.

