### Secondary Outcomes

The secondary outcomes of the study will be defined as follows:

Compliance: intake of at least 70% (41/58) sachets of study intervention volume.Overall complications: occurrence of any postoperative complication (major or minor) from surgery following each patient’s hospital stay and up to 90 days from the initial operation. Occurrence of any postoperative infections will also be calculated.CCI at 90 days from the index surgery will be determined for each patient. This index can be calculated for each patient using the CCI Web-based calculator [26,30] following the grading of each postoperative complication according to the Clavien-Dindo classification [31].QoL: The global health-related QoL at baseline, 1 month, and 3 months following randomization will be measured using the European Organization for Research and Treatment of Cancer Quality of life Questionnaire [32,33] instrument and the Functional Assessment of Cancer Therapy-General scale [34].Length of hospital stay will be determined for each patient.

Compliance with the intervention is a secondary objective and will be taken into consideration for the success of its feasibility, as modifications to the protocol may be needed if compliance is poor. Compliance will be measured as the percentage volume of prescribed study intervention consumed, which will be measured by a patient diary in the preoperative period and nurses’ charts in the postoperative period. Postoperative complications (major or minor) will be determined following each patient’s hospital stay and up to 90 days from the initial operation. This is classified according to Clavien-Dindo classification [26,31,35].

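### Compliance is defined by sachet count in one section and by percentage of volume in another, with no rule for a partly consumed sachet, so one patient can be classed both ways

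*Protocol article*

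**What the plan says.** The protocol article defines compliance in three places.

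- **Statistical Analysis** uses a count. "Good compliance will be defined as consumption of ≥70% (at least 41/58) sachets of the study intervention before and after surgery". The lower side of the cut is also a count: "Compliance of <70% (40/58 sachets or less) will be considered poor, and reasons for noncompliance will be further explored".
- **Secondary Outcomes** gives a measurement rule in volume: "Compliance will be measured as the percentage volume of prescribed study intervention consumed". Its own outcome line mixes the units: "Compliance: intake of at least 70% (41/58) sachets of study intervention volume".
- **Abstract, Results** mixes them too: "intake of at least 70% (41/58) sachets of the intervention volume".

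Both kinds of data are to be collected. Before surgery, the compliance form holds "the number of packets the patient took every day, the volume that was ingested, the days it was ingested for" (Administration). In hospital, the nurses' log records the amount taken at each administration, and Data Management describes "a specific CRF designed to record the volume of the supplement the patient has taken after surgery".

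The article does not say whether a partly consumed sachet counts, or how volume converts to sachets.

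**The concern.** A count of sachets and a percentage of volume are different scales. They agree only if every serving is taken whole or not at all and all servings have the same volume. Neither condition is assured. Servings are 250 or 400 mL drinks, and the protocol itself lists bad taste, side effects and inability to tolerate oral intake as possible reasons for noncompliance. Volume is also not a fixed quantity for the protein supplement: "Each serving delivers 20 g of protein stirred into a minimum of 250 mL of liquid or soft foods".

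Compliance is the first secondary objective. Secondary Outcomes says that it will be weighed in judging feasibility and may lead to protocol modifications. The 70% cut also decides whether reasons for noncompliance are explored; at or above it, Statistical Analysis plans no such exploration. If the class depends on which sentence the analyst follows, so do the reported proportion compliant and that follow-on analysis.

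**Working it through.** **Inputs.** ISOlution: one serving a day, ending on the sixth day before surgery, at least 250 mL each (ISOlution section); packets are labelled from day 30 before surgery (Blinding). INergy-FLD: three doses a day for five days before and five days after surgery, 250 mL each. PreCovery: three servings of 400 mL.

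**Reproducing 41/58.** Protein from day −30 to day −6 is 25 servings; INergy-FLD is 3 × 10 = 30; PreCovery is 3. The total is 25 + 30 + 3 = 58, as stated. Then 0.70 × 58 = 40.6, so the smallest passing count is 41 (41/58 = 70.7%; 40/58 = 69.0%). The stated figures are right for this schedule.

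**Volume of the same schedule.** Taking ISOlution at its 250 mL minimum: 55 × 250 + 3 × 400 = 13,750 + 1,200 = 14,950 mL, and 70% of this is 10,465 mL. ISOlution supplies 25 × 250 = 6,250 mL, or 41.8% of the total, so a large part of the volume denominator rests on that assumption.

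**Partial intake.** Suppose a patient drinks the same fraction f of every serving. The volume score is then f, whatever the mixing volumes.

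| f | Volume | By volume | Count, started sachets | Count, finished sachets |
|---|---|---|---|---|
| 0.60 | 8,970 mL (60%) | poor | 58/58, good | 0/58, poor |
| 0.80 | 11,960 mL (80%) | good | 58/58, good | 0/58, poor |

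If started sachets count, the rules conflict for every f above 0 and below 0.70. If only finished sachets count, they conflict for every f from 0.70 to just under 1.

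**Whole servings only.**

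| Sachets | PreCovery among them | Volume | % of 14,950 | By count | By volume |
|---|---|---|---|---|---|
| 40 | 3 | 37 × 250 + 1,200 = 10,450 | 69.9 | poor | poor |
| 41 | 0 | 41 × 250 = 10,250 | 68.6 | good | poor |
| 41 | 1 | 40 × 250 + 400 = 10,400 | 69.6 | good | poor |
| 41 | 2 | 39 × 250 + 800 = 10,550 | 70.6 | good | good |
| 41 | 3 | 38 × 250 + 1,200 = 10,700 | 71.6 | good | good |
| 42 | 0 | 42 × 250 = 10,500 | 70.2 | good | good |

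The rules disagree only in the second and third rows.

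**The denominator.** The count uses a fixed 58; the volume rule uses what was prescribed. The operation is to take place within 4 weeks of enrollment (Study Agents). If protein starts 28 days before surgery, it covers days −28 to −6, which is 23 servings, and the total is 23 + 33 = 56. Forty-one sachets is then 41/56 = 73.2%. At 21 days the total is 16 + 33 = 49 and 41 is 83.7%. The fixed count therefore asks for more than 70% of these patients' own schedules.

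**The case against.** The best defence is that there is only one rule, loosely worded. The mixed phrases in the abstract and in Secondary Outcomes can be read as treating 41/58 as the sachet equivalent of 70% of the prescribed intervention, with volume as the way intake is measured. Recording volume both before and after surgery fits that reading, and the scoring of part-used sachets could be left to a fuller document that is not shown. This reading is possible, but Statistical Analysis applies 41 and 40 as counts on either side of the cut, and the whole-serving table shows that the count is not equivalent to 70% of volume. A fuller document could supply a missing detail; it would still have to choose between two rules that the article states.

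Three further points on that side stand. First, a reader might infer that sachet counting overstates exposure, or that anyone who partly drinks every serving is fully compliant by count. The documents do not support either: the text speaks of consumption, not of opening a sachet, and if only finished sachets count the error runs the other way. Second, the whole-serving conflict is a narrow edge, one count value short by at most 1.4 percentage points. Third, the numeric stop, modify or continue rule uses only the proportion randomized, and the documents give no figure for how common partial intake will be.

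**Conclusion.** The concern holds as an inconsistency in the definition of a secondary outcome. Two stated rules, in different units and with different denominators, can put the same patient on opposite sides of the 70% cut. With partial intake the conflict can be complete (58/58 against 60%, or 0/58 against 80%). Its direction cannot be settled from the article, because that depends on whether a started or only a finished sachet counts. With whole servings it is confined to exactly 41 sachets with no or one PreCovery serving.

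The volume figures assume 250 mL per ISOlution serving and the 58-serving schedule. The effect on the proportion compliant cannot be estimated, since the documents give no distribution of intake. The primary feasibility criterion is untouched. The point should be corrected because compliance is weighed in the feasibility judgement and its cut controls whether reasons for noncompliance are examined.

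**What to change.** Use one measure in the abstract Results, Statistical Analysis and Secondary Outcomes:

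- Score each prescribed serving by the fraction ingested, from 0 to 1, taken from the diary before surgery and the nurses' log after it.
- Compliance is the sum of these fractions divided by the number of servings prescribed to that patient, given the actual interval from randomization to surgery.
- Apply the 70% cut to that percentage. Drop 41/58, 40/58 and the references to total volume.

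Replacing the fixed 58 is a change of substance and should be stated as such. The plan should also say whether servings withheld under an order to suspend administration stay in the denominator.

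The cost is small: wording in three places, using packets and amounts that are already to be recorded. The diary may need a fraction-taken entry for ISOlution, because a volume cannot be turned into a fraction when the powder is mixed into soft food or a variable amount of liquid. Reported compliance may rise or fall relative to a sachet count. The change is best made before any compliance data are scored.

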**Methods:**

This is a double-blind randomized placebo-controlled feasibility trial. The intervention comprises three nutritional supplements: a protein isolate powder (ISOlution); immunomodulation (INergy-FLD), formulated liquid diet; and carbohydrate loading (PreCovery). Patients will consume 1 serving of the protein supplement per day from the randomization time up to 6 days before surgery (30 days in total). The immunomodulation, a solution that contains arginine, protein isolate, omega-6 fatty acids, and RNA, aims to attenuate excessive inflammatory responses and to replenish nutrients. This solution will be consumed as 3 doses per day for 5 days before and after surgery. Carbohydrate loading helps to reduce the stress from surgery by decreasing insulin resistance. Patients will have 2 servings the evening before surgery and 1 serving 2-3 hours before surgery. To be eligible, patients must have a resectable gastrointestinal cancer for which an elective operation is planned. Patients will be stratified according to nutritional status. The operation should occur within 4 weeks from enrollment.

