### Study Agents

#### Nutritional Supplements and Placebo

Patients undergoing gastrointestinal cancer surgery will either receive perioperative nutritional supplements or placebo (Multimedia Appendix 1). The operation should occur within 4 weeks from study enrollment. Upon assessment, patients will have a consultation with their physician where standard recommendations on nutrition prior to their surgery will be provided. This consultation will happen in the B3 wing or the Surgical Oncology Clinics of JHCC. Immediately following randomization (same day), patients will receive the intervention or placebo. The intervention consists of the following 3 different solutions.

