#### Immunomodulation-Formulated Liquid Diet (INergy-FLD)

In preparation for surgery, patients will consume an immune-modulating formula containing various ingredients, including arginine, protein isolate, omega-6 fatty acids, and RNA, aimed to attenuate excessive inflammatory responses without being immunosuppressive and to replenish nutrients that are depleted in a state of stress (ie, surgery), thereby enhancing the recovery process [1]. The volume of this solution is 250 mL per dose (51 g of powder reconstituted in 250 mL of cold water). Patients will be asked to consume 3 doses per day for 5 days prior to surgery and 5 days following surgery.

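### The fixed 41-of-58-sachet compliance cut-off asks for more than 70% of what a patient operated on within 4 weeks is prescribed, and cannot be met at all after a wait of 12 days or less

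*Protocol article*

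**What the plan says.** The compliance rule is a fixed count. Statistical Analysis says "Good compliance will be defined as consumption of ≥70% (at least 41/58) sachets of the study intervention before and after surgery" and adds "Compliance of <70% (40/58 sachets or less) will be considered poor". Secondary Outcomes repeats the count: "Compliance: intake of at least 70% (41/58) sachets of study intervention volume". The Results paragraph of the abstract uses it too.

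Later in Secondary Outcomes a different measure appears: "Compliance will be measured as the percentage volume of prescribed study intervention consumed". Its denominator is what the individual patient was prescribed.

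The schedule is given under Study Agents:

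- Protein isolate: one serving a day, "from the time of randomization up to 6 days before surgery (up to 30 days in total". The abstract has "from the randomization time up to 6 days before surgery (30 days in total", without the words that make 30 a maximum.
- Immunomodulation formula: "Patients will be asked to consume 3 doses per day for 5 days prior to surgery and 5 days following surgery".
- Carbohydrate loading: two servings the evening before surgery and one on the day.
- Timing: "The operation should occur within 4 weeks from study enrollment". Study product is handed over on the day of randomization, and no minimum wait is stated.

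Under Blinding, the packets are described as labelled from 30 days before surgery to 5 days after it.

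**The concern.** Only the protein component varies in length, and it runs from randomization. A patient with a shorter wait is asked to take fewer sachets, yet is judged against the same 58. The 70% in the rule is then not 70% of that patient's prescription. The true requirement rises as the wait shortens, until it exceeds what was supplied for use.

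Completion of the supplement program is the first secondary objective. Secondary Outcomes says that compliance will be considered in judging feasibility and that poor compliance may lead to protocol modifications. Statistical Analysis also makes the exploration of reasons for noncompliance depend on this threshold. A measure pulled down by surgical scheduling could point to a problem with the supplements that does not exist, or give a larger trial a compliance figure that is too low.

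**Working it through.** **Inputs, all from Study Agents.** Let T be the days from randomization to surgery, with intake starting on the day of randomization.

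- Protein isolate, day −T to day −6: T − 5 sachets (T from 5 to 30)
- Immunomodulation formula: 3 × 5 + 3 × 5 = 30
- Carbohydrate loading: 2 + 1 = 3

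Prescribed total = (T − 5) + 30 + 3 = T + 28.

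**Reproducing the article's figures.** At T = 30: 25 + 30 + 3 = 58. The cut-off is 0.70 × 58 = 40.6, rounded up to 41 (41/58 = 70.7%; 40/58 = 69.0%). Both figures reproduce, but only with a 30-day lead-in, which matches the packet labels. At the 4-week limit, T = 28 gives 56.

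**What 41 means at other waits.**

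| T (days) | Prescribed (T + 28) | 41 ÷ prescribed | 70% of own prescription, rounded up |
|---|---|---|---|
| 30 | 58 | 70.7% | 41 |
| 28 | 56 | 73.2% | 40 |
| 21 | 49 | 83.7% | 35 |
| 14 | 42 | 97.6% | 30 |
| 13 | 41 | 100% | 29 |
| 12 | 40 | not reachable | 28 |
| 7 | 35 | not reachable | 25 |

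At T = 12, perfect intake is 40 sachets, which the article classes as poor. If intake starts the day after randomization, the total is one lower for waits of 6 to 30 days: 55 at 28 days, and 41 is out of reach at 13 days or less.

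**The two stated measures disagree.** A patient with T = 14 who takes 35 of 42 sachets has taken 35/42 = 83% of the prescription, but 35/58 = 60% on the fixed count. The first is good compliance and the second is poor.

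**Size under stated assumptions.** The article gives no distribution of waits. Assume that each sachet is taken independently with probability 0.85 and that T is uniform over whole days in a range. For each T, the fixed rule classes a patient compliant with probability P(X ≥ 41), and the patient-specific rule with probability P(X ≥ 0.70 × (T + 28)), where X is binomial with T + 28 trials and probability 0.85. Averaging over T:

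| Range of T (days) | Compliant by 41/58 | Compliant by 70% of own prescription |
|---|---|---|
| 7–28 | 40% | 99% |
| 14–28 | 58% | more than 99% |
| 21–28 | 90% | more than 99% |
| 24–28 | 97% | more than 99% |

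These are scenarios, not estimates for this center.

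**The case against.** The strongest reply is that the operative rule is 70% and that 41/58 only illustrates it for a full course. The article attaches fractions to percentages elsewhere: the feasibility thresholds are written over 100, although about 165 eligible patients are expected. The statement about prescribed volume would then govern, and it is close to the remedy proposed here. This does not stand. Statistical Analysis spells out at least 41 as good and 40 or fewer as poor, so an analyst following that section would apply the counts. At best, the article gives two incompatible definitions.

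Other parts of the reply do stand:

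- The 4-week limit is worded as a target, so a patient who waits 30 days and is prescribed 58 is not ruled out.
- At 28 days the shortfall is only two sachets.
- The stop, modify or continue rule uses only the proportion randomized.
- Both arms face the same cut-off, so the harm is mainly to the overall compliance figure.
- Packets taken per day and reasons for noncompliance are recorded, so the cause could be found and the measure recalculated.

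A reader might also take the abstract's 30 days to mean 30 protein sachets and a total of 63. The full text makes 30 a maximum, so this is loose wording in the abstract and not a second denominator. Nor is protein volume undefined because the mixing liquid is given only as a minimum: the serving is fixed at 20 g of protein.

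**Conclusion.** The fixed count is wrong as written. For every wait of 28 days or less it demands more than 70% of what the patient was asked to take, and it contradicts the article's own percentage-of-prescription measure. These conclusions follow from the stated schedule alone. The direction of the error is certain: for such waits, compliance is understated.

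The size is not known. It runs from a few percentage points if nearly all waits are close to 4 weeks to a very large effect if waits of one to two weeks are common. The scenario percentages rest on the assumed waits and the assumed 85% independent intake.

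Two stronger readings are tempting. One is that short-wait patients in general fail even with perfect intake. That is true only at 12 days or less (13 with a next-day start); from 13 to 28 days the bar is too high but can be met. The other is that the outcome mostly measures waiting time. Without a distribution of waits the article cannot support that, and the 24-to-28-day scenario shows almost no effect.

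**What to change.** Define compliance for each patient as sachets consumed divided by sachets prescribed for that patient's actual randomization-to-surgery interval, with good compliance at 70% or more. Delete the 41/58 and 40/58 counts from the abstract's Results, Statistical Analysis and Secondary Outcomes. Use one unit throughout, for example sachet equivalents with a part-consumed serving counted as a fraction, so that the volume statement and the threshold describe the same quantity.

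Separately, the sponsor should reconcile the abstract's 30 days in total, the full text's maximum of 30 days, the packet labels starting 30 days before surgery, and the 4-week timing of the operation. Changing the compliance definition does not alter dosing.

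The cost is a wording change before analysis. The diary and nurses' log already record daily packets and amounts, and the denominator needs only the randomization and surgery dates.
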